## Abstract

**Background:**

Smoking is a strong risk factor for cancer and atherosclerosis. Cancer mortality, especially from lung cancer, overtakes cardiovascular (CV) death rate in patients with peripheral arterial disease (PAD). Only a few patients with lung cancer after PAD management may benefit from surgical excision. Circulating tumor cells (CTC) associated with low-dose chest CT (LDCT) may improve early cancer detection. This study focuses on a screening strategy that can address not only lung cancer but all tobacco-related cancers in this high-risk population.

**Methods:**

DETECTOR Project is a prospective cohort study in two French University hospitals. Participants are smokers or former smokers (≥30 pack-years, quitted ≤15 years), aged ≥55 to 80 years, with atherosclerotic PAD or abdominal aortic aneurysm. After the first screening round combining LDCT and CTC search on a blood sample, two other screening rounds will be performed at one-year interval. Incidental lung nodule volume, volume doubling time and presence of CTC will be taken into consideration for adapted diagnostic management. In case of negative LDCT and presence of CTC, a contrast enhanced whole-body PET/CT will be performed for extra-pulmonary malignancy screening. Psychological impact of this screening strategy will be evaluated in population study using a qualitative methodology. Assuming 10% prevalence of smoking-associated cancer in the studied population, a total of at least 300 participants will be enrolled.

**Discussion:**

Epidemiological data underline an increase incidence in cancer and related death in the follow-up of patients with PAD, compared with the general population, particularly for tobacco-related cancers. The clinical benefit of a special workup for neoplasms in patients with PAD and a history of cigarette smoking has never been investigated. By considering CTCs detection in this very high-risk selected PAD population for tobacco-induced cancer, we expect to detect earlier pulmonary and extra-pulmonary malignancies, at a potentially curable stage.

**Trial registration:**

The study was registered in the French National Agency for Medicines and Health Products Safety (No N° EUDRACT_ID RCB: 2016-A00657–44) and was approved by the ethics Committee for Persons Protection (IRB number 1072 and n° initial agreement 2016-08-02; ClinicalTrials.gov identifier NCT02849041).

## Background

In European countries, cancer has now overtaken cardiovascular disease as the main cause of death [1]. Smoking is considered as a major risk factor for atherosclerosis and cancer and remains the predominant risk factor for premature death in Europe [2]. In patients with peripheral arterial disease (PAD), mortality rate from cancer is currently exceeding that of cardiovascular diseases [3]. Lung cancer is considered as the most frequent cause of death from cancer in Europe [4]. Most patients with tobacco related cancer present with advanced disease, not yet curable with currently available therapies. Therefore, early detection might be a valuable approach to detect the disease at an asymptomatic and potentially curable stage.

The clinical relevance of lung cancer screening in a population with PAD has been first underlined in 1983 in patients referred for peripheral vascular surgery [5]. Recent epidemiological evidence confirms that PAD as well as abdominal aortic aneurysm (AAA) are markers for the development of lung cancer [6–8], independently of age [9, 10]. Because of an advanced disease stage at the time of diagnosis, only a few patients with lung cancer after atherosclerotic vascular disease management may benefit from surgical excision [11]. Selection of patients with prevalent atherosclerotic peripheral disease may thus dramatically increase the benefit of cancer screening.

Early diagnosis of lung cancer is of paramount importance in terms of prognosis [12]. The US National Lung Screening Trial (NLST) pointed out that early lung cancer diagnosis has the potential to improve survival. A screening strategy with low-dose chest CT (LDCT) showed a 20% reduction in lung cancer-related deaths and an overall all-cause mortality reduction of 6,7% in participants with a history of cigarette smoking [13]. Results of the European NELSON study which proposed a screening protocol based on nodule volume measurement and growth rate confirms NLST results (as recently presented at the 2018 World Conference on Lung Cancer showing a reduction of lung cancer deaths by 26% in men and up to 39% in women).

However, LDCT screening focuses only on lung cancer, ignoring all other smoking related cancers (head and neck, esophagus, stomach, liver, colon, pancreas, kidney, bladder, ovary, uterine cervix and myeloid leukemia) [14]. On the other hand, strong concerns have been raised about possible harmful consequences of screening: false positive results requiring repeated and potential invasive procedures among participants without cancer, theoretical risk of radiation – induced carcinoma, and a poorly known psychological impact of screening procedures [15]. Screening should thus be applied to a population at high risk of smoking induced cancer.

Presence of circulating tumor cells (CTC) is considered as a sensitive biomarker for early metastatic cascade, cancer progression and drug treatment monitoring [16]. The Isolation by Size of Epithelial Tumor cells (ISET) technology is a blood filtration-based approach that has the potential to detect circulating non-hematologic cells [17]. Clinical data highlighted that these cells can be isolated in the blood stream before cancer was detectable on imaging [18].

In order to address not only lung cancer but all tobacco-related cancers in smokers and ex-smokers suffering from atherosclerotic PAD and/or AAA, the DETECTOR study will analyze the interest of CTC detection associated with LDCT for an early detection of cancers associated with PAD. The psychological part of the study will focus on emotional and psychosocial impact on participants of this screening strategy, and particularly those psychosocial mechanisms involved in the search of CTC. The psychological research team will also assess physician communication strategies.

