## Methods/design

### Study design

DETECTOR project is a multicentric prospective cohort study, funded by the French National Cancer Institute, the National League against Cancer and the Foundation for Cancer Research, in a collaborative effort of Paris Descartes University associated hospitals and Paris Diderot University. This trial intends to evaluate unenhanced LDCT in combination with the detection of CTC, in the screening of smoking-associated cancers in patients with PAD or AAA as well as the psychological impact of this screening strategy.

After inclusion in the trial, participants will undergo the first round of screening. Participants without prevalent cancer at baseline will undergo two other screening rounds at one-year interval each, combining LDCT and CTC search on a blood sample (Table 1). Participants will be followed for a total of at least 3 years after inclusion.

**Table 1 Tab1:** Study flow chart of examinations

Actions	V0: baseline visit	within 1 m after V0	V0 + 5w	V1(V0 + 1y)	V1 + 5w	V2(V0 + 2y)	V2 + 5w
Information	✓						
Informed consent	✓						
Verification of inclusion and exclusion criteria	✓						
Enrolment	✓						
Psychologist presence^(1)^	✓						
Personal and family medical history^(2)^	✓						
Ongoing treatments	✓			✓		✓	
Socio-demography	✓						
Level of tobacco use	✓						
Screening round: - Blood sampling for CTC detection - LDCT	✓			✓		✓	
Results of the screening round			✓		✓		✓
Psychological counselling^(3)^		✓	✓	✓			
Clinical events since last visit^(2)^				✓		✓	
Adverse events	✓		✓	✓	✓	✓	✓

1: as an observer; 2: focused on cancer and vascular diseases; 3: only for patients who are volunteer to participate at the psychological study

The study sponsor is Paris Saint-Joseph Hospital. The study was registered in the French National Agency for Medicines and Health Products Safety (No N° EUDRACT_ID RCB: 2016-A00657–44) and was approved by the ethics Committee for Persons Protection (Comité de Protection des Personnes Ile de France II, IRB number 1072 and n° initial agreement 2016-08-02). The total duration of the trial is 6 years (inclusion period = 36 months; follow-up = 3 years; ClinicalTrials.gov identifier NCT02849041). Prolonged follow-up of trial participants will be performed each year after the end of the scheduled trial period. The first study participant has been enrolled on January 2017; last patient’s enrollment is expected on December 2019.

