### Objectives

The primary objective of the study is to determine the diagnostic value of the couple LDCT combined with CTC search for the early detection of smoking associated cancers in a cohort of asymptomatic but high-risk participants presenting with PAD and/or AAA.

The secondary objectives are (1) to describe detected malignancies with this screening strategy and to evaluate patient’s survival, (2) to evaluate the rate of detection of CTCs in the study population, (3) to study the effect of smoking cessation program on patient’s decision to quit smoking, (4) to study the emotional and psychosocial impact of this screening strategy and more specifically related to CTC detection, (5) to assess, adjust and improve communication strategies of health professionals.

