### Management of incidental findings

First-line screening incidental findings and adapted screening strategy are displayed in Table 2. In case of negative LDCT or incidental lung nodule(s) with a volume < 50 mm^3^ and absence of CTCs, this screening strategy will be repeated once a year for a total of 3 consecutive rounds. Participants will be excluded from further screening when diagnosed with lung cancer or extra-pulmonary malignancy. In case of incidental lung nodule(s) with a volume > 500 mm^3^, in the presence or absence of CTCs, a specific multidisciplinary team meeting will discuss diagnostic and pre-therapeutic evaluation for lung cancer [23]. In case of incidental lung nodule(s) with a volume between 50 and 500 mm^3^ and presence of CTCs, diagnostic and pre-therapeutic evaluation for lung cancer will also be performed. In the absence of CTCs, volume doubling time - evaluated through a second LDCT performed three months later - will be taken into consideration for adapted diagnostic management. In case of negative LDCT or incidental lung nodule(s) with a volume < 50 mm^3^, and presence of CTCs, a contrast enhanced whole-body scanner and PET/CT associated with clinical head and neck examination and cytological examination of the urine will be performed for extra-pulmonary malignancy screening and management (Fig. 1).

**Table 2 Tab2:** First-line screening incidental findings and adapted screening strategy

Low –dose chest CT and search for CTCs	No incidental lung nodule or nodule(s) <50mm^3^	Incidental lung nodule(s) with volume between 50 and 500mm^3^	Nodule(s) >500mm^3^
No CTC	Next screening round at one year	Measure of volume doubling time at low-dose chest CT 3 months later	Diagnostic and pretherapeutic evaluation
Presence of CTC	Contrast enhanced whole-body scanner and PET/CT examination of the head and neck cytological examination of the urine	Diagnostic and pretherapeutic evaluation	Diagnostic and pretherapeutic evaluation

*CTC: circulating tumor cells; PET/CT: Positron emission tomography-computed tomography*

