### Statistical analysis and sample size

Data will be analyzed using SAS and R software. Alpha level for statistical significance (p) will be set at less than 5%. Characteristics of the study population will be described as mean plus or minus standard deviation for continuous variables with a normal distribution and as median [interquartile range] for skewness distribution. Categorical variables will be described as numbers and proportions. Student’s t-test or nonparametric Wilcoxon test will be used to compare quantitative parameters between different groups of patients and Chi2 test or Fischer test for qualitative parameters.

The primary outcome will focus on the sensibility and specificity of the screening strategy associating detection of CTCs and LDCT. Statistical analysis is in accordance with the STARD (Standards for Reporting of Diagnostic Accuracy Studies) guidelines [24]. To meet the primary objective, sensitivity will be estimated by dividing the number of patients diagnosed by the CTC method by the number of patients with lung cancer confirmed by the reference technique, i.e. LDCT. The results will be expressed with a binomial proportion 95% confidence interval. Specificity will be estimated by dividing the number of patients diagnosed with CTC as cancer-free with the number of patients without lung cancer. Secondary evaluation criteria will be analyzed using the same statistical methods as those used for the primary endpoint.

Assuming 10% prevalence of smoking-associated cancer in the studied population [8], if we aim to study a total of at least 30 detected cancers, including baseline and repeat screening rounds, we need to enroll a total of at least 300 participants.

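### CTC specificity is scored against LDCT-confirmed lung cancer with no role for follow-up, so a CTC result that runs ahead of imaging counts as an error

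*Protocol article*

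**What the plan says.** All references are to the protocol article.

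- **Background.** The reason for adding CTC search is that "Clinical data highlighted that these cells can be isolated in the blood stream before cancer was detectable on imaging".
- **Objectives.** The aim is to "determine the diagnostic value of the couple LDCT combined with CTC search for the early detection of smoking associated cancers", so the target is wider than lung cancer.
- **Statistical analysis and sample size.** "The primary outcome will focus on the sensibility and specificity of the screening strategy associating detection of CTCs and LDCT". The denominator for sensitivity is the "number of patients with lung cancer confirmed by the reference technique, i.e. LDCT". For specificity: "Specificity will be estimated by dividing the number of patients diagnosed with CTC as cancer-free with the number of patients without lung cancer". Neither formula mentions follow-up, and predictive values are not named.
- **Management of incidental findings.** For a CTC-positive participant with a negative LDCT or only a nodule below 50 mm³, "a contrast enhanced whole-body scanner and PET/CT associated with clinical head and neck examination and cytological examination of the urine will be performed", to look for cancer outside the lung. The section does not say how a participant with a negative work-up is classified.
- **Study design.** Rounds are at baseline, 1 year and 2 years. "Participants will be followed for a total of at least 3 years after inclusion". Yearly follow-up beyond the scheduled period is also announced, without a link to the accuracy analysis.

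**The concern.** The hypothesis is that CTCs can signal a cancer before a scan shows it. If so, some CTC-positive participants will have a clean LDCT on the day and a cancer later. A reference made of LDCT alone cannot recognise them, and the specificity formula leaves them among patients without lung cancer as CTC errors. The same happens to a CTC-positive participant whose extra-pulmonary cancer is found by the trial's own work-up.

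The lead that the trial sets out to study is thus scored against the test. A low specificity could mean that CTC search is non-specific, or that the reference was too narrow and too early, and the planned analysis could not tell these apart.

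**Working it through.** **1. The plan's own figure.** Target cancers / assumed prevalence = 30 / 0.10 = 300, which reproduces. It leaves 300 - 30 = 270 participants without cancer, used as the base below. The sample size itself does not bear on this point.

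**2. Specificity when later cancers are left out.** The documents give no CTC-positive rate, sensitivity or lead time, so these inputs are assumed. Let FP be the CTC-positives among the 270 and L the number of those who carry a latent cancer.

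- As scored: (270 - FP) / 270
- With later cancers recognised: (270 - FP) / (270 - L)

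| Apparent FP rate | FP | Latent share | L | As scored | Recognised | Loss (points) |
|---|---|---|---|---|---|---|
| 3% | 8.1 | 10% | 0.81 | 97.0% | 97.3% | 0.3 |
| 5% | 13.5 | 25% | 3.375 | 95.0% | 96.2% | 1.2 |
| 5% | 13.5 | 50% | 6.75 | 95.0% | 97.4% | 2.4 |
| 10% | 27 | 50% | 13.5 | 90.0% | 94.7% | 4.7 |

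The direction depends on one condition: latent cancers must be proportionally commoner among CTC-positives than among CTC-negatives. If 10% of both groups were latent, the 5% case would give (256.5 × 0.9) / (270 × 0.9) = 95.0%, unchanged. The Background premise implies that the condition holds.

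**3. Confirmed extra-pulmonary cancers under the stated formula.** Assume a true specificity of 95% (13.5 false positives in 270), E extra-pulmonary cancers among the 30, and a share s of these CTC-positive. Patients without lung cancer number 270 + E, and the formula gives 1 - (13.5 + sE) / (270 + E).

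- E = 10, s = 0.5: 1 - 18.5/280 = 93.4%
- E = 20, s = 0.8: 1 - 29.5/290 = 89.8%

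This loss of about 1.6 to 5.2 points needs no lead time at all.

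**4. If follow-up is used but no window is fixed.** Minimum time after a draw = 3 years minus the time of the round. If lead time is exponential with mean m years (assumed), the share still unconfirmed after w years is exp(-w/m).

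| Round | Minimum time left | Rounds still to come | m = 1 | m = 2 | m = 3 |
|---|---|---|---|---|---|
| 1 (V0) | 3 years | 2 | 5% | 22% | 37% |
| 2 (V1) | 2 years | 1 | 14% | 37% | 51% |
| 3 (V2) | 1 year | 0 | 37% | 61% | 72% |

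**5. How long a common window must be.** In Table 1, V1 is one year after V0 and its results come 5 weeks later. A 12-month window from the V0 draw could close before the next round reports, so the window must exceed 12 months plus 5 weeks. For V2 the guaranteed follow-up is 36 - 24 = 12 months, which falls short of that. The yearly prolonged follow-up is therefore needed for round 3.

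**The case against.** The strongest reply is that a condensed article commonly leaves the follow-up window and the handling of unconfirmed positives to the full protocol or SAP, neither of which is shown. That stands for the missing window, which alone would be no finding. It does not cover the reference technique and the two formulas, which the article states and which conflict with its rationale and its primary objective.

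Some stronger readings are tempting, but the text does not support them:

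- **A reader might infer that CTC-positives become false positives once a window closes, and that this window shrinks by round.** No such rule is written. The 3, 2 and 1 years are minimums inferred from Study design. The formulas count patients, not tests, and only diagnosed cancers end screening. A V0 or V1 positive therefore has further LDCTs, and a lung cancer found on one of them might be credited. The inequality is sharpest for round 3.
- **A reader might take Table 1, which ends 5 weeks after V2, as the end of follow-up.** Study design promises at least 3 years, so this reading fails.
- **A reader might stress predictive value, where the shift could be large.** It is not a planned measure.
- **A reader might conclude that sensitivity is understated too.** That follows only if later cancers arise solely in CTC-positives. Any among CTC-negatives pull sensitivity down.

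The bias may also be modest beside sampling error: the exact 95% interval for 256/270 is 91.5% to 97.1%. That is a fair limit on its importance, but a wider sample would not remove the bias.

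**Conclusion.** The point holds in this form. Followed as written, the analysis scores CTC results against LDCT-confirmed lung cancer and treats a positive that precedes imaging, or that reflects cancer outside the lung, as an error. The expected direction is understated specificity, given the protocol's own premise that latent cancers concentrate among CTC-positives.

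The size is unknown. The ranges shown (0.3 to 4.7 points for later cancers, 1.6 to 5.2 points for confirmed extra-pulmonary ones) rest wholly on assumed rates and illustrate the order of magnitude only. The unequal time for confirmation is a second, conditional problem: it arises if follow-up is brought in without a common window. The correction is worth making before analysis.

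**What to change.** In Statistical analysis and sample size:

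1. Replace the LDCT-only reference with a composite of diagnostic work-up plus follow-up for any smoking-associated cancer, applied identically to CTC-positive and CTC-negative participants.
2. State one window, counted from each blood draw and equal for all rounds, long enough to take in the next annual round and its results. Use the announced yearly prolonged follow-up to complete it for V2.
3. Classify CTC-positive, work-up-negative participants as unconfirmed until the window closes.
4. Report round 3 separately. Equal length does not give equal ascertainment when no LDCT follows V2.
5. Give specificity at last follow-up as a sensitivity analysis.

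The cost is analysis wording and use of follow-up already planned. Final status for round-3 positives would come a year or more after V2. A common window shorter than 3 years also gives up confirmation time for round 1: with an assumed mean lead time of 2 years, 61% of latent cancers are unconfirmed at 1 year against 22% at 3 years, which is why item 5 is needed. A longer window, in turn, may credit some unrelated new cancers to an old CTC result, so its length should be justified when it is stated.

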## Methods/design

### Study design

DETECTOR project is a multicentric prospective cohort study, funded by the French National Cancer Institute, the National League against Cancer and the Foundation for Cancer Research, in a collaborative effort of Paris Descartes University associated hospitals and Paris Diderot University. This trial intends to evaluate unenhanced LDCT in combination with the detection of CTC, in the screening of smoking-associated cancers in patients with PAD or AAA as well as the psychological impact of this screening strategy.

After inclusion in the trial, participants will undergo the first round of screening. Participants without prevalent cancer at baseline will undergo two other screening rounds at one-year interval each, combining LDCT and CTC search on a blood sample (Table 1). Participants will be followed for a total of at least 3 years after inclusion.

**Table 1 Tab1:** Study flow chart of examinations

Actions	V0: baseline visit	within 1 m after V0	V0 + 5w	V1(V0 + 1y)	V1 + 5w	V2(V0 + 2y)	V2 + 5w
Information	✓						
Informed consent	✓						
Verification of inclusion and exclusion criteria	✓						
Enrolment	✓						
Psychologist presence^(1)^	✓						
Personal and family medical history^(2)^	✓						
Ongoing treatments	✓			✓		✓	
Socio-demography	✓						
Level of tobacco use	✓						
Screening round: - Blood sampling for CTC detection - LDCT	✓			✓		✓	
Results of the screening round			✓		✓		✓
Psychological counselling^(3)^		✓	✓	✓			
Clinical events since last visit^(2)^				✓		✓	
Adverse events	✓		✓	✓	✓	✓	✓

1: as an observer; 2: focused on cancer and vascular diseases; 3: only for patients who are volunteer to participate at the psychological study

The study sponsor is Paris Saint-Joseph Hospital. The study was registered in the French National Agency for Medicines and Health Products Safety (No N° EUDRACT_ID RCB: 2016-A00657–44) and was approved by the ethics Committee for Persons Protection (Comité de Protection des Personnes Ile de France II, IRB number 1072 and n° initial agreement 2016-08-02). The total duration of the trial is 6 years (inclusion period = 36 months; follow-up = 3 years; ClinicalTrials.gov identifier NCT02849041). Prolonged follow-up of trial participants will be performed each year after the end of the scheduled trial period. The first study participant has been enrolled on January 2017; last patient’s enrollment is expected on December 2019.

